#### Secondary outcomes

##### Quality of life

The Manchester Short Assessment of Quality of Life (MANSA; 16 items, self-report) is a shortened version of the Lancashire Quality of Life Profile (LQLP) [46]. It reliably measures quality of life in patients with psychological problems [47].

##### Recovery

The Individual Recovery Outcomes Counter (I.ROC; 12 items, interview) has been found to be a valid and reliable measure of recovery in mental health [48].

##### Social and community functioning

To obtain information regarding social and community functioning, several self-report questions (DEM_2) on education, work, social network and frequency and quality of social contact will be included.

##### Role functioning

The World Health Organization Disability Assessment Schedule-36 items (WHODAS 2.0-36, interview) produces reliable disability measures across six domains to assess general, social and community functioning [49–51].

##### Global functioning

The global assessment of functioning scale (GAF) and the social and occupational functioning scale (SOFAS) will be derived from DSM Axis V to assess global functioning and symptom severity (GAF) and social functioning (SOFAS) [52–55]. The interviewer, who is blind for condition, will administer both scales after each measurement.

##### Clinical symptoms

The Brief Symptom Inventory-18 items (BSI-18; self-report) is a validated, reliable instrument for assessing general psychopathological symptoms as an index of severity of syndromal disorders [56–58]. As well as the total score, a dimensional score on somatic complaints, depression and anxiety will be obtained.

##### Attachment

The Revised Adult Attachment Scale (RAAS, 18 items, self-report) has moderate to good psychometric properties for assessing attachment style [59–61].

##### Satisfaction with care

Patients’ appreciation of care will be assessed using the Client Satisfaction Questionnaire (CSQ-8) [62] supplemented with the relative’s involvement dimension of the Verona Service Satisfaction Scale (VSSS-EU) [63]. The CSQ-8 is a one-dimensional 8-item instrument for assessing global patient satisfaction. It has demonstrated high construct validity and internal consistency reliability [64], also in Dutch [65]. The relative’s involvement dimension of the VSSS-EU consists of six items that cover various aspects of the patient’s satisfaction with help given to his/her closest relative. Also, four self-formulated questions were added, two covering the degree of patients’ satisfaction with the role of their relatives in their treatment, and two covering patients’ satisfaction with the collaboration of the various services involved.

#### Cost-effectiveness

##### Cost data and quality of life

The Trimbos and Institute of Medical Technology Assessment Cost Questionnaire for Psychiatry (TIC-P, interview) estimates use of care services, use of medication, and the amount of work loss (absenteeism and reduced efficiency) [66]. The questionnaire will be adapted to fit the purpose of this study and uses a 3-month recall period.

The 5-level EuroQol 5 dimensions (EQ-5D-5L) is a standardized non-disease-specific instrument that will be used to obtain utility scores on the basis of social tariffs, expressed in Dutch unit prices [67, 68].

#### Significant others

##### Burden of significant others (filled in by significant others)

The Involvement Evaluation Questionnaire (IEQ, 31 items, self-report) assesses the consequences of mental illness for significant others [69, 70]. It will be sent online to the significant others who are proposed by the patient.

#### Sample size

Power calculations of the study will be based on the earlier described meta-analysis investigating the effectiveness of RACT [31]. Using the program G*power (two-sided, power = 80%, alpha = 0.05; G*power 3.1) with a medium effect size (*d* = 0.5) [31], we found that a total of 126 participants would be sufficient to detect a statistically significant difference between the two conditions. If account is taken both of repeated measures within a person (assuming a within-correlation of 0.6) and of clustering of data (teams; assuming an intraclass correlation coefficient (ICC) of 0.05, health centers; assuming an ICC of 0.1), a sample of N = 133 is needed. To account for possible drop-outs (rate 35%), we aim to recruit a total sample of N = 180. Eighteen teams at a total of nine Dutch mental health centers will participate, each with two teams. In principle, each team should deliver a mean of N = 10 patients per team over the course of 1 year.

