### Part one: effectiveness study

#### Study design

Patients in this multisite RCT will be randomly allocated either to RG method plus FACT or to standard FACT (ratio 1:1). Randomization will be performed at individual patient level. Data for both conditions will be collected at baseline and after 9 and 18 months (follow-up assessments). For an overview of the flow of screening procedures and assessments, see Fig. 1. Importantly, since FACT teams do almost all outpatient care in the Netherlands for SMI patients, it was not possible to have a second control group without FACT.

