##### Randomization and blinding

Randomization will be performed on an individual level. A statistician from the Trimbos Institute, who will be independent from the research team, will perform the randomization using a computer-generated concealed-randomization sequence stratified on teams. To keep randomization unpredictable, the sequence will contain variable-allocation block sizes [37], in which two sizes of allocation blocks (i.e., 2 and 4) are randomized. Assuming ten participants per team, this results in three possibilities for block size 4 (i.e., 2 × 4; 1 × 4; 0 × 4). To minimize the risk of imbalance between conditions, the ratio of these sequences will be stratified on respectively 1:2:2. The allocation sequence will be stored by the independent statistician and be concealed from all researchers, care providers and participants. Participants will be allocated after baseline measurement. Once they have been allocated, the researcher and local staff will be informed of the condition by email. Further matching between patient and case-manager will be performed by the local FACT team staff and will be based on condition. That is, when participants are allocated to the RG condition, care providers trained in the RG procedures will be the case-manager. Patients in the control condition can have any FACT care providers as their case-manager.

Assessments comprise self-report questionnaires, and structured and semi-structured interviews (see Table 3). They will take place at the participants’ homes or any other location they prefer. An independent and blinded interviewer will guide them through the self-report questionnaires and will conduct the interviews. The interviewer will bring a laptop and- using a unique login-code- will assess the questionnaires online, then securing them on an encrypted server (Jambo). If participants are unable to use the laptop, they will fill in the questionnaires on paper and the interviewer will then later enter the data into the online environment.

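### The adjusted sample size of 133 cannot be traced to all of its stated inputs under individual randomisation stratified by team

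*Protocol article*

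**What the plan says.** All references are to the protocol article.

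- **Sample size, first step.** The settings are "two-sided, power = 80%, alpha = 0.05; G*power 3.1", "with a medium effect size" of d = 0.5. The result is that "a total of 126 participants would be sufficient".
- **Sample size, second step.** Repeated measures enter by "assuming a within-correlation of 0.6", and clustering by "clustering of data (teams; assuming an intraclass correlation coefficient (ICC) of 0.05, health centers; assuming an ICC of 0.1". With these, "a sample of N = 133 is needed". No formula is shown.
- **Sample size, third step.** A 35% dropout rate leads to a target of 180, from 18 teams in nine centres (two teams each), with a mean of 10 patients per team.
- **Study design.** "Randomization will be performed at individual patient level", in a 1:1 ratio, with assessments at baseline, 9 and 18 months.
- **Randomization and blinding.** Allocation uses a "computer-generated concealed-randomization sequence stratified on teams". RG patients are given a case-manager trained in the method; control patients may have any care provider of the team.
- **Analyses.** A mixed model has observations, patients, teams and centres as its levels.

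**The concern.** Stratifying individual randomisation by team puts both arms in every team and every centre. A shift shared by all patients of a team or centre then falls on both arms alike and drops out of the treatment difference. The usual repeated-measures factors at a correlation of 0.6 also reduce the required number. On the stated design, then, both kinds of adjustment should bring 126 down, yet the text reports an increase to 133. If the ICCs were instead meant as design effects for randomised clusters, a centre ICC of 0.1 with some 20 patients per centre should push the figure far above 133.

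What is at stake is the meaning of the 80% power claim. The figure of 133 is the benchmark from which the recruitment target is derived. If it does not describe this design, the reader cannot tell what power the trial has at the number expected to be analysed.

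**Working it through.** **Inputs from the article.** Two-sided alpha 0.05, power 80%, d = 0.5, within-person correlation 0.6, team ICC 0.05, centre ICC 0.1, 10 patients per team (so 20 per centre), three assessments, dropout 35%. Normal approximation throughout.

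**1. The base figure.** Per arm, 2 × (1.960 + 0.842)² / 0.5² = 62.8, so 63 per arm and 126 in total. The stated figure reproduces. (The exact t-test gives 128; the argument does not depend on which is used.)

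**2. Repeated-measures factors at r = 0.6.**
- Baseline-adjusted single follow-up: 1 − 0.6² = 0.64
- Mean of three assessments: (1 + 2 × 0.6)/3 = 0.733
- Mean of two follow-ups: (1 + 0.6)/2 = 0.8; change from baseline: 2 × (1 − 0.6) = 0.8

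**3. The design as stated.** Three treatments of the common team and centre variance are shown: no factor; team variance removed (1 − 0.05 = 0.95); both removed (1 − 0.05 − 0.10 = 0.85).

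| Repeated-measures factor | No clustering factor | × 0.95 | × 0.85 |
|---|---|---|---|
| 0.64 | 80.6 | 76.6 | 68.5 |
| 0.733 | 92.4 | 87.8 | 78.5 |
| 0.8 | 100.8 | 95.8 | 85.7 |

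The range is about 69 to 101. A baseline-adjusted mean of both follow-ups (factor 0.8 − 0.36 = 0.44) would need fewer still: 126 × 0.44 = 55.4.

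**4. Both ICCs as cluster-randomisation design effects.**
- Variance components, 10 per team and 20 per centre: 1 + 9 × 0.05 + 19 × 0.10 = 3.35. Then 126 × 0.64 × 3.35 = 270 and 126 × 0.8 × 3.35 = 338.
- Nested form: 1 + 9 × 0.05 + 10 × 0.10 = 2.45. Then 126 × 0.64 × 2.45 = 198, 126 × 0.733 × 2.45 = 226 and 126 × 0.8 × 2.45 = 247.
- Nested form with 133/18 = 7.39 per team: 1 + 6.39 × 0.05 + 7.39 × 0.10 = 2.06. Then 126 × 0.64 × 2.06 = 166.

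Milder conventions exist. Treating a centre as a cluster of two teams gives 1.45 × 1.1 = 1.595, hence 126 × 0.64 × 1.595 = 129 and 126 × 0.733 × 1.595 = 147.

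**5. Routes that come close to 133.**
- 126 × 0.733 × (1 + 9 × 0.05) = 126 × 0.733 × 1.45 = 134.0. Team ICC only.
- 126 × 0.8 × (1 + 6.39 × 0.05) = 126 × 0.8 × 1.32 = 133.0. Team ICC only; the 7.39 per team is itself derived from 133.
- 126 × 1.05 = 132.3 and 126/0.95 = 132.6. Both round up to 133, with the within-person correlation and the centre ICC unused.
- 126 × 0.44 × 2.45 = 135.8. Uses every input, but misses 133 and still treats teams and centres as randomised.

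**6. Power at the expected number analysed.** 180 × 0.65 = 117. Power = Φ(0.5 × √(117/4) / √factor − 1.96), where 0.5 × √(117/4) = 2.704.
- Factor 1: Φ(2.704 − 1.96) = 77%
- Factor 0.8: Φ(3.023 − 1.96) = 86%
- Factor 0.64: Φ(3.380 − 1.96) = 92%

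**7. Illustration of RG-arm clustering.** The article gives no figure for this. Assume that the two ICCs act within the RG arm alone, with 5 RG patients per team and 10 per centre.
- Team level only: RG-arm factor 1 + 4 × 0.05 = 1.2, averaging 1.1 over the arms. Required number 126 × 0.8 × 1.1 = 111; power at 117 is Φ(2.704/√0.88 − 1.96) = 82%.
- Both levels: 1 + 4 × 0.05 + 9 × 0.10 = 2.1, averaging 1.55. Required number 126 × 0.8 × 1.55 = 156; power at 117 is Φ(2.704/√1.24 − 1.96) = 68%.

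**The case against.** Four points can fairly be made for the plan.

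**Back-fitting does not identify a method.** Several routes land on or near 133, so a reader might infer that the planners ignored the centre ICC or treated teams as randomised. The article does not establish either. This stands: only the lack of a traceable path from inputs to figure can be claimed.

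**The adjustments need not always lower the number.** RG patients see only trained case-managers, and the Training in the RG method section requires as few as two trained members per team, so outcomes in that arm may cluster despite individual randomisation. This also stands. Step 7 shows that the required number can then pass 133. But the article attaches its ICCs to teams and centres, not to case-managers or to variation in the treatment effect, so it does not present 133 as an allowance for this.

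**The figure is cautious.** For the stated design 133 exceeds what steps 2 and 3 require. This stands, with the proviso on RG-arm clustering, and it limits the consequence.

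**A condensed article may leave the formula and the primary time point to other documents.** Agreed; neither omission is the point here, and which time point to power is for the planners to settle. What remains is a number said to take account of specific inputs that, under the stated design, do not lead to it.

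**Conclusion.** The point holds in a limited form: 133 is not supported by its stated inputs together with the stated design. The design gives about 69 to 101. Cluster-type inflation with both ICCs mostly gives about 166 to 338 for repeated-measures factors of 0.64 to 0.8, although the mildest conventions go lower. The simplest routes to 133 leave the centre ICC of 0.1 unused.

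A reader might infer that the trial is underpowered, since 117 evaluable is below 133. The documents do not support that: at d = 0.5, power at 117 is about 86% to 92% with repeated-measures factors of 0.8 to 0.64, and falls to 77% only if no such gain is counted. Equally, they do not show adequate power if RG-arm clustering is material, because they give no figure for it.

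The conclusion assumes equal team sizes, an equal correlation of 0.6 between all assessments and, for the 69 to 101 range, no treatment-by-team or case-manager clustering. The 0.85 factor also takes d = 0.5 as standardised on the total variance and 0.6 as the correlation within teams. If 0.6 includes the shared variance, the lowest cell becomes 126 × (0.85 − 0.45²/0.85) = 77, still inside the range.

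**What to change.** In the Sample size section:

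1. Restate the calculation for individual randomisation within teams, without design-effect inflation for common team and centre effects. Say how each ICC enters, or remove it.
2. Name the contrast that is powered and the repeated-measures factor that goes with it, and use the same factor throughout.
3. Add a sensitivity range for treatment-by-team variation and for case-manager clustering in the RG arm, with the assumed values stated.
4. Report power at the 117 evaluable patients left from 180 at 35% dropout.

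The cost is a recalculation and a few sentences. Enrolment of 180 need not change on this account, nor do the randomisation and the analysis model.

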**Methods/design:**

This multisite randomized controlled trial will compare the effects of the RG-method integrated in Flexible Assertive Community Treatment (FACT) (90 patients) with those of standard FACT (90 patients). Baseline assessments and 9-month and 18-month follow-up assessments will be conducted in face-to-face home visits. The primary outcome measure, empowerment, will be assessed using the Netherlands Empowerment List (NEL). The secondary outcomes will be quality of life (MANSA); personal, community and clinical recovery (I.ROC); general, social and community functioning (WHODAS 2.0); general psychopathological signs and symptoms (BSI-18); and societal costs (TiC-P). An economic evaluation of the cost-effectiveness and cost utility of the RG method will also be conducted. A qualitative multiple case-study will be added to collect patients’, RG members’ and professionals’ perspectives by in-depth interviews, observations and focus groups.

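### Recruiting 180 does not cover 35% drop-out against a need of 133: it leaves 117 with complete follow-up and covers at most 26% loss

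*Protocol article*

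**What the plan says.** All the figures are in the Sample size section of the protocol article.

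- The starting calculation is "two-sided, power = 80%, alpha = 0.05; G*power 3.1", "with a medium effect size" of d = 0.5. Its result is given as: "we found that a total of 126 participants would be sufficient to detect a statistically significant difference between the two conditions".
- The section then allows for repeated measures ("assuming a within-correlation of 0.6") and for clustering by team ("assuming an intraclass correlation coefficient (ICC) of 0.05") and by centre ("health centers; assuming an ICC of 0.1"). This gives a requirement of 133.
- Last comes the drop-out step: "To account for possible drop-outs (rate 35%), we aim to recruit a total sample of" 180.

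The same section describes 18 teams with a mean of 10 patients each. The abstract (Methods/design) gives the same total by arm: "the RG-method integrated in Flexible Assertive Community Treatment (FACT) (90 patients) with those of standard FACT (90 patients").

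Two other sections bear on the point. Study design places follow-up at 9 and 18 months. Analyses specifies multilevel mixed regression on everyone randomised, with observations nested within people.

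**The concern.** A drop-out rate is a share of those recruited. At 35%, 65% of the recruited patients remain, so the requirement has to be divided by 0.65. The step from 133 to 180 is too small for that. It is the size obtained by adding 35% of the requirement to itself, a common slip.

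The sample-size statement is what readers use to interpret the primary empowerment (NEL) result. As written, it tells them that the required number survives a 35% loss. If the comparison turns out null with drop-out near that rate, the result would be read against a margin that the plan's own inputs do not provide.

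**Working it through.** **Inputs, all from Sample size:** two-sided alpha 0.05, power 80%, d = 0.5, base N 126, required N 133, drop-out 35%, target 180. The 1:1 allocation is from Study design.

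**1. Base figure.** By the normal approximation, n per arm = 2 × (1.960 + 0.8416)² / 0.5² = 62.8, so 63 per arm and 126 in total. This matches the plan. (The noncentral t gives 64 per arm, 128 in total, which is close enough not to matter here.)

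**2. The plan's target.**
- 133 × (1 + 0.35) = 179.55, rounded up to 180. This matches.
- 133 / (1 − 0.35) = 204.6, rounded up to 205. This does not match.
- Starting from 126: 126/0.65 = 193.8 (194) and 126 × 1.35 = 170.1 (171). Neither matches.
- 18 teams × 10 patients = 180. This also matches.

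**3. What 180 delivers.**
- Complete follow-up at 35% drop-out: 180 × 0.65 = 117.
- Shortfall: 133 − 117 = 16, or 12% of the requirement. 117 is also below the unadjusted 126.
- Largest drop-out at which 133 remain: 1 − 133/180 = 26.1%.
- Recruitment that retains 133 at 35%: 205, or 206 for equal arms, which is 25 or 26 more than 180.

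**4. Power if drop-outs contribute nothing.** Take 133 as the 80% point, as the plan does.
- Power at 117 = Φ(2.8016 × √(117/133) − 1.960) = Φ(0.668) = 0.748, about 75%. The noncentral t gives about 74%.
- Effect detectable with 80% power: 0.50 × √(133/117) = 0.53.

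**5. Power if drop-outs contribute as much as they can.** The article does not say when patients are expected to drop out. As the favourable extreme, assume that all 63 lost patients (180 − 117) have a 9-month value, that the contrast is at 18 months, and that the correlation is the plan's 0.6.
- Effective N = 180 / (0.6² + (1 − 0.6²)/0.65) = 180 / (0.36 + 0.9846) = about 134. By the formula in step 4, power is about 80%.
- With baseline adjustment, the partial correlation is (0.6 − 0.36)/(1 − 0.36) = 0.375. Effective N = 180 / (0.1406 + 0.8594/0.65) = about 123, and power is about 77%.

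The loss of power at 35% drop-out therefore lies between about 0 and 5 percentage points, depending on when patients leave and on the form of the model.

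**The case against.** The strongest objection concerns the analysis. The mixed model covers all randomised patients and uses every available observation, so a patient seen at 9 months and lost by 18 months still contributes. A reader might infer from the arithmetic that only 117 patients can be analysed, or that 80% power is simply lost. The Analyses section supports neither. 117 is the number with complete follow-up, and step 5 of the working shows that the loss of power could be close to zero.

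That part of the objection stands, but it does not reconcile the printed figures. The plan's inflation step treats drop-outs as lost and sets 133 as the number needed after them. Nowhere does it say that partial data justify a smaller inflation. Repeated measures were already counted in reaching 133, so the same gain cannot be claimed again in full. Patients lost before 9 months have no post-baseline value at all.

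A second objection is that the article states no inflation formula. Multiplication by 1.35 is a close inference, but 18 teams of 10 patients also make 180, so the target may be partly logistical. That stands too, and the route to 180 should not be stated as fact. The mismatch with 35% is the same by either route.

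A third is that the power figure depends on 133 being a sound 80% point. The step from 126 to 133 cannot be uniquely reproduced from the stated inputs: averaging three measures at a correlation of 0.6 (factor 0.733) with a team design effect of 1 + 9 × 0.05 = 1.45 gives 126 × 0.733 × 1.45 = 134, but leaves out the centre ICC. The 75% is therefore conditional on the plan's own 133. The shortfall of 16 and the 26% limit do not depend on the power calibration; they compare the plan's 133 and 180 directly.

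**Conclusion.** The point holds as an inconsistency among three printed figures: 133 needed, 35% drop-out, 180 recruited. On those figures 180 covers at most 26% drop-out, and at 35% it leaves 117 patients with complete follow-up, 16 short. Nothing in the article gives the rate another meaning.

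The consequence for power is modest and conditional. It is about 75% rather than 80% if 133 is the 80% point and drop-outs supply no outcome data. It is nearer 80% if most of them supply a 9-month value. The documents do not support a flat statement that the trial lacks 80% power.

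**What to change.** Keep N = 180 and replace the drop-out sentence in Sample size with wording such as:

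*N = 180 retains the required 133 patients if drop-out is at most 26%; at 35% drop-out, 117 have complete follow-up and power is about 75% under the same assumptions if drop-outs contribute no outcome data.*

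The cost is one sentence and a slightly less favourable statement of power. There is no extra enrolment and no change to allocation or analysis. The 90 + 90 in the abstract agrees with 180 and needs no edit. A target of 205 (206 for equal arms) is needed only if the sponsor wants 133 patients with complete follow-up at 35% drop-out.

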#### Analyses

Outcome data will be analyzed using multilevel mixed regression models with 4 levels: observations within people, people within teams, and teams within centers. Analyses will be conducted on the entire randomized sample (i.e., intention to treat). Supplementary analysis will be done on the completers sample. A completer will be defined after further inspection of the frequency of the RG meetings to define a minimum of attendance of a RG meeting during a 12-month period after the first assessment. In future publications the number of minimum RG meetings will be clearly stated within the definition of a completer and included in the consort flow chart of the RCT. To analyze potential between-condition differences in baseline characteristics (such as gender and diagnosis), we will use Student’s t-tests for continuous variables and Pearson Chi-squared tests for categorical variables. As a covariate, the analysis will include variables that show different distributions in the conditions (p ≥ 0.05 difference at baseline) and are correlated with the results. For categorical outcome variables we will choose counts and, if there are non-normal residuals, appropriate forms of mixed regression (such as binomial, Poisson and gamma). All analyses will be carried out using SPSS version 20+ and/or R version 3.0+. Results will be described in accordance with the CONSORT guidelines for randomized controlled trials [35].

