#### Study procedures

##### Recruitment

Patients will be recruited at nine mental healthcare organizations throughout the Netherlands, each of which will participate with minimum two FACT teams. Care providers of the FACT team will screen patients on the basis of the inclusion and exclusion criteria (see Fig. 1). After informing eligible patients of the RG procedures and the study, care providers will then ask them to participate. To this end, patients will receive oral and written information about the RG model and an information letter outlining the trial procedures, explaining confidentiality, and providing the contact details of the research team. Interested patients will be given a week to consider their participation.

The above described procedure for screening and informing patients about the study will be performed on two different groups of patients: either new patients entering a FACT team (i.e., during the intake phase); or a randomly generated selection of patients who have already been in FACT for no more than 24 months. For the latter, we will use an online tool (http://www.randomizer.org), to randomly select patients who have been recently (24 months) added to the caseload of the case-managers trained in the RG method. Importantly, these two routes are used to screen and inform a representative sample of the FACT population of the study. After patients sign informed consent, the researcher will perform an extra check on the inclusion and exclusion criteria and an independent interviewer will contact the participant to make the first appointment for the baseline assessment. After completing the assessment, participants will receive a gift voucher worth €15,-.

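### The supplementary completer analysis sets its attendance cut-off after looking at attendance, on a criterion only RG patients can meet, over a window that runs 3 months past the 9-month outcome

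*Protocol article*

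**What the plan says.** The Analyses section of the protocol article makes intention to treat, on everyone randomised, the main approach. It then adds: "Supplementary analysis will be done on the completers sample". The completer rule is left open: "A completer will be defined after further inspection of the frequency of the RG meetings", the purpose being "to define a minimum of attendance of a RG meeting during a 12-month period after the first assessment". Disclosure comes later: "In future publications the number of minimum RG meetings will be clearly stated within the definition of a completer", and the number is also to appear in the CONSORT flow chart.

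Four other places bear on this rule:

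- Under Study design, outcomes are collected at baseline, 9 months and 18 months.
- Under Recruitment, the first assessment is the baseline one: "an independent interviewer will contact the participant to make the first appointment for the baseline assessment". Under Randomization and blinding, allocation follows it.
- Under Resource group plus FACT, RG meetings are a component of that arm, usually three-monthly, with a frequency that may vary. In the Discussion, trained staff are told to keep RG elements out of standard FACT.
- No completer rule is given for control patients.

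**The concern.** Three features of the rule combine.

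- **The cut-off follows the data.** The minimum is chosen once observed meeting frequency is known. A full 12-month attendance record cannot exist for a patient until after that patient's 9-month visit, so 9-month NEL data can already be in hand when the cut-off is chosen. The article does not say that whoever chooses it will be kept from those data.
- **Only one arm can be selected.** Attendance is a post-randomisation variable that exists in the RG arm alone. Whatever controls are used, they cannot be selected on the same behaviour, so the two groups are no longer made comparable by randomisation.
- **The window overruns an outcome.** Behaviour after the 9-month assessment would help decide who counts in a 9-month comparison.

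If attendance is related to prognosis, the analysis can show a difference between arms when there is no treatment effect, or mask one. If the intention-to-treat result is null or marginal, a completer result would be printed beside it and could carry weight that it does not deserve.

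**Working it through.** The article gives no completer threshold, completion rate or completer-set power, so there is no stated figure to reproduce. The timing follows from the text; the size of any bias can only be illustrated.

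**Timing (from the document)**

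- The window runs from month 0 to month 12; outcomes fall at months 9 and 18.
- Part of the window after the 9-month outcome: 12 − 9 = 3 months, or 3/12 = 25%. On a three-monthly schedule that is about one of four meetings.
- Part of the window after the 18-month outcome: none. It closes 18 − 12 = 6 months earlier.

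**Is selection plausible? (from the document)**

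- Pointing to better-placed patients attending more: unresolved issues between members can delay meetings. Also, 13 of the 40 NEL items (7 social support, 6 connectedness) concern matters close to the ability to convene a group.
- Pointing the other way or to neither: meeting frequency follows needs and wishes, so patients with greater needs may meet more often. A patient with little or no network still starts with a minimal group of patient, case manager and psychiatrist.
- Some selection is plausible; its sign is not settled.

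**Size (assumed inputs)**

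Let p be the share of RG patients who complete and g the prognostic gap between completers and non-completers in SD units. With no treatment effect, and all controls as comparator (also an assumption):

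spurious difference = completer mean − arm mean = (1 − p) × g

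- p = 0.7, g = 0.3: 0.3 × 0.3 = 0.09 SD
- p = 0.6, g = 0.5: 0.4 × 0.5 = 0.20 SD
- p = 0.5, g = 0.5: 0.5 × 0.5 = 0.25 SD

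Against the planned d = 0.5 this is 0.09/0.5 = 18% to 0.25/0.5 = 50%.

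If the gap is already present at baseline and the analysis adjusts for baseline, the within-person correlation of 0.6 assumed under Sample size leaves 1 − 0.6 = 0.4 of it:

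- 0.4 × 0.09 = 0.036, about 0.04 SD
- 0.4 × 0.25 = 0.10 SD

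A fully stable gap would cancel in a comparison of change scores.

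**Cross-check by simulation**

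20,000 trials per scenario, 90 per arm, no treatment effect, RG completers against all controls, unadjusted two-sided t-test at 0.05. Completers are the top share p on an attendance propensity with correlation ρ to the outcome; the analytic bias is ρ × φ(z₁₋ₚ)/p.

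| ρ | p = 0.85: bias, type I error | p = 0.70: bias, type I error | p = 0.50: bias, type I error |
|---|---|---|---|
| 0 | 0.00 SD, 5% | 0.00 SD, 5% | 0.00 SD, 5% |
| 0.2 | 0.05 SD, 6% | 0.10 SD, 9% | 0.16 SD, 14% |
| 0.3 | 0.08 SD, 8% | 0.15 SD, 15% | 0.24 SD, 25% |

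Without an attendance–outcome link there is no bias. A negative ρ would reverse the sign. These error rates belong to an unadjusted test, not to the planned mixed model.

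**The case against.** The strongest reply is that nothing important depends on this analysis. It is labelled supplementary, the intention-to-treat analysis and its error rate are untouched, and the article promises to disclose the cut-off. All of that stands and limits the severity. It does not repair the rule, and it cannot be set aside as detail left to a fuller document, because the article itself commits to defining the set after inspection.

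A reader might go further and infer three things that the documents do not support:

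- **That the cut-off will be tuned to the result.** The inspection named is of meeting frequency, which is exposure and not outcome. The article does not rule out a choice made with outcomes in view, but it does not describe one.
- **That the analysis must favour the RG arm.** The section on the RG intervention contains pointers both ways, so it could favour either arm.
- **That completers will be set against all controls.** This is the natural reading, but the article gives no rule for controls. The loss of randomised comparability does not depend on it.

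The timing problem is also narrow. It affects only a 9-month completer comparison, and the article does not say at which visit the completer analysis will be reported.

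**Conclusion.** The point holds as a defect of a supplementary analysis. As written, the completer set is defined after its own exposure data have been inspected, on a post-randomisation criterion available in one arm, with 3 of its 12 months falling after the 9-month outcome. The comparison is therefore non-randomised and could be biased.

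The illustrative range is about 0.04–0.25 SD. It rests on assumed completion of 50–70%, an assumed gap of 0.3–0.5 SD, and whether the gap is present at baseline and adjusted for. The true bias could be zero or of opposite sign. The primary conclusion of the trial is not at risk. Severity: minor to moderate.

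**What to change.** 1. State the minimum number of RG meetings before any follow-up NEL data are seen. The usual three-monthly schedule allows this without trial data: it implies about 9/3 = 3 meetings by month 9 and 18/3 = 6 by month 18.
2. Replace the window "during a 12-month period after the first assessment" with attendance up to the visit analysed, 9 or 18 months, with a minimum for each. The RG meeting form, completed after every meeting, already supplies the counts.
3. Say how control patients enter the comparison, and report it as descriptive and non-randomised. Steps 1 and 2 remove the data-dependent cut-off and the use of post-outcome attendance; they do not remove selection.
4. Optionally, add a complier-average causal effect estimate that keeps all randomised patients, as a sensitivity analysis only. It assumes that allocation does nothing for patients below the cut-off. The section on the RG intervention undermines this by describing empowerment during preparation, before any meeting. For illustration, take 60% completers, an intention-to-treat effect of 0.30 SD and a benefit of 0.20 SD in non-completers. The true completer effect is (0.30 − 0.4 × 0.20)/0.6 = 0.37 SD, but the estimator returns 0.30/0.6 = 0.50 SD. The doubt should be stated, and a second uptake definition that includes preparation could be shown. The standard error also grows by roughly 1/0.6 = 1.67 in this example.

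The cost is a paragraph of wording, a little extra analysis, and the loss of freedom to choose the cut-off later.
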